### Health economic analysis

The primary within trial analysis will be a cost-effectiveness analysis which will estimate the incremental cost per reduction in respiratory support (initiated within 72 hours after birth, ie, the study primary outcome), with the time horizon spanning from birth to child hospital discharge or 28 days, whichever is sooner.

The costs of the intervention will be calculated as the daily cost of ACS medication and the associated administration costs. Hospital attendances required to administer ACS will be included. The direct medical costs post birth will be calculated based on resource utilisation accruing for the care of new born (after birth respiratory treatment; admission to neonatal care) and women (type of delivery, inpatient stays; hospital transfers, etc) including adverse events. Resource utilisation for woman and child will be collected from the clinical hospital records up to 28 days post birth.

The mean cost and mean outcome associated with the intervention and the control arm will be estimated using generalised linear model, which will tackle non-normality of data, adjusting for relevant covariates (eg, type of delivery; MC/DC twins) and adjusting for women-level clustering, in line with the statistical analysis.

If evidence of differences between the treatment arms in terms of effectiveness, costs or cost-effectiveness are found in the trial, a decision analytic model will be developed to explore the cost-effectiveness of ACS administration over a medium (2 year) and longer term (lifetime) horizon. The medium term analysis will use data from the final trial follow-up period in childhood (eg, PARCA-R, any medical records available, etc), to account for costs and consequences which are associated with ACS treatment over the neonatal period (hypoglycaemia; neonatal health) and childhood (mortality; cognitive development metabolic illness).

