ACS are not devoid of harm. A large RCT of ACS in late preterm singletons demonstrated an increase in neonatal hypoglycaemia in the ACS group compared with placebo (number needed to harm 11).^9^ ACS have well-recognised detrimental effects on fetal growth (birth weight, length and head circumference) and conflicting results on neurodevelopment. Three studies (one RCT follow-up and two longitudinal studies) have shown detrimental effects on neurodevelopment following ACS exposure,^4 5 10^ but a recently published prospective follow-up study of the above RCTs of ACS in late preterm singletons demonstrated no adverse effect of ACS on childhood neurodevelopment outcomes.^11^ The balance of risk and benefit needs to be determined for twin pregnancies. Reducing term (>37 weeks gestation) neonatal care admission is a UK national priority. It poses a high cost to the NHS and separation of mothers and babies is detrimental to maternal well-being, mother–infant bonding and breastfeeding.^12^ There is evidence that ACS reduce serious respiratory morbidity and neonatal unit admission but there is potential for short (eg, hypoglycaemia) and long-term harms (eg, neurodevelopment). Either currently a substantial number of babies miss a morbidity sparing treatment; or a substantial number receive a potentially harmful treatment unnecessarily as practice varies substantially across the UK. STOPPIT-3 will provide the evidence to address this uncertainty.

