#### Secondary outcomes

Severe respiratory morbidity within 72 hours after birth (defined as one or more of the following: CPAP or high-flow nasal cannula for at least 12 continuous hours; supplemental oxygen with a fraction of inspired oxygen of at least 0.30 for at least 24 continuous hours; mechanical ventilation; ECMO; stillbirth; neonatal death within 72 hours of birth).Any admission to neonatal care (ie, admission for any reason and for any duration).Neonatal care admission within 72 hours of birth for 48 hours or more or any neonatal care admission (within 28 days of birth) or those requiring surfactant treatment or nitric oxide therapy.Apgar score at 5 min.Umbilical arterial cord pH.Umbilical arterial cord base excess.Newborn hypoglycaemia diagnosed within 48 hours of birth (defined as blood glucose of less than 2.0 mmol per litre).Newborn neonatal jaundice (defined as those requiring treatment with phototherapy according to NICE threshold for gestation and postnatal age).Birth weight centile.Head circumference at birth.All cause early onset sepsis within 72 hours of birth (defined as culture positive (pure growth from blood or CSF of a known bacterial pathogen) or culture negative (acute onset of illness with three or more predefined clinical signs)).Extended perinatal mortality (stillbirth or neonatal death up to 28 days).Stillbirth (death in utero).Neonatal death (death within 28 days of birth).Exclusive breastmilk nutrition at discharge.Confirmed or suspected maternal postpartum infection during hospital admission (defined by a new prescription of antibiotics, confirmed systemic infection on culture or endometritis as defined by the US Centres for Disease Control and Prevention).Cost effectiveness of treatment with ACS compared with placebo.Childhood cognitive and language development at 2 years of age determined by the Parent Report of Children’s Abilities-Revised (PARCA-R) score^14^ (in the first 340 women recruited to the trial).

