### Randomisation

Randomisation to ACS or placebo will be performed immediately prior to administration, 24 hours to 120 hours before the planned birth. Randomisation is performed using a web-based randomisation system managed by Edinburgh Clinical Trials Unit (ECTU) via a web portal. Users will be assigned a unique study identifier and will be required to enter minimal patient details prior to randomisation. As this is a large trial (1552 women), group imbalances are unlikely therefore a simple allocation sequence with no minimisation criteria will be used. Study participants, trial investigators and medical staff providing care will remain blinded to treatment allocation. The randomisation process will assign each participant with a study drug treatment pack number and the first dose of IMP should be given immediately following randomisation with the second dose administered 24 hours (±4 hours) after the first dose. Participants will be allocated to receive either:

Corticosteroid group—two doses of 12 mg dexamethasone by IM injection 24 hours (±4 hours) apart.Placebo group—two doses of matching placebo (sodium chloride 0.9%) by IM injection 24 hours (±4 hours) apart.

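### The within-trial cost-effectiveness horizon closes at the child's discharge although resource use is planned to day 28, so post-discharge costs fall outside it at a cut-off that treatment may move

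*Protocol article*

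**What the plan says.** All from the protocol article.

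- **Horizon** (Health economic analysis). The primary within-trial analysis estimates incremental cost per reduction in respiratory support, "with the time horizon spanning from birth to child hospital discharge or 28 days, whichever is sooner".
- **Intervention costs** (same section, next paragraph). "The costs of the intervention will be calculated as the daily cost of ACS medication and the associated administration costs". It adds: "Hospital attendances required to administer ACS will be included".
- **Data collection** (same section). "Resource utilisation for woman and child will be collected from the clinical hospital records up to 28 days post birth".
- **Timing of treatment** (Randomisation). "Randomisation to ACS or placebo will be performed immediately prior to administration, 24 hours to 120 hours before the planned birth".
- **Clinical outcomes on a 28-day frame** (Secondary outcomes). One admission outcome includes "any neonatal care admission (within 28 days of birth"; neonatal death and extended perinatal mortality also run to 28 days.
- **Expected effect on neonatal care** (Introduction). "There is evidence that ACS reduce serious respiratory morbidity and neonatal unit admission". The Introduction also reports more hypoglycaemia with ACS in late preterm singletons.

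**The concern.** A costing window should be the same length in both arms and should not depend on what treatment does. This one closes at discharge for any child who goes home before day 28. Discharge follows randomisation, and the protocol itself expects ACS to affect neonatal admission. Costing time may therefore differ between arms, and it can differ between two babies of one pregnancy. The woman's costs, which the section also counts, would be cut off at a child's discharge.

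At stake is the within-trial cost per respiratory-support event avoided. Cost-effectiveness is a stated aim of the trial, in the Abstract and under Design. If one arm has more hospital use between discharge and day 28, the horizon as written would not see it, although the plan appears to collect the data that would show it.

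The other end of the window is a smaller matter. It opens at birth, while treatment and the attendances to give it come earlier.

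**Working it through.** The plan gives no cost, length-of-stay or readmission figure, so there is nothing of its own to reproduce here. The check compares the statements and then shows algebraically what is left out.

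**1. End of the window.** The horizon ends at min(discharge, day 28). Resource use for woman and child is to be collected to day 28, and that sentence mentions no stop at discharge. The secondary outcomes count neonatal admission and death to day 28. As an illustration, a baby discharged on day 4 and readmitted to neonatal care on day 12 would be a clinical event within 28 days, would have resource use recorded, and would fall outside the costing horizon.

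**2. Whose discharge.** The rule refers to the child. Each pregnancy has two babies, who may go home on different days, and a woman whose costs have no end date of their own under the rule.

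**3. Start of the window.** Measured from planned birth, treatment starts at −120 to −24 hours, and the horizon opens at 0. Read literally, that puts drug, administration and attendance costs outside it, yet the next sentences count them. The two statements conflict in wording.

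**4. What the end rule omits.** Write total cost per baby as C = I + S + R, where

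- I is the antenatal intervention cost,
- S is the hospital cost from birth to discharge (or day 28), and
- R is the hospital cost from discharge to day 28.

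With Δ meaning ACS minus placebo:

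- full incremental cost to day 28: ΔC = ΔI + ΔS + ΔR
- incremental cost under the stated horizon, with antenatal costs included as intended: ΔI + ΔS
- amount omitted: ΔR

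So the error is ΔR. It is zero if post-discharge costs are equal in the two arms, whichever arm goes home first. A shorter index stay is a real saving, already captured in ΔS.

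**5. Effect on the ratio.** The effect side (support within 72 hours) is largely unaffected. Take the planned absolute difference of 12% − 8% = 4 percentage points (Statistical analysis and sample size), which is 40 events avoided per 1000 babies. The ratio then moves by ΔR / 0.04.

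The documents give no readmission rates, so those below are **assumptions**. They cover baby readmissions only, and c is an unknown cost per readmission.

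| Assumed readmission, placebo | ACS | Uncounted difference per 1000 babies | Shift per support event avoided |
|---|---|---|---|
| 3% | 3% | 30 − 30 = 0 | 0 / 40 = 0 |
| 3% | 4% | 40 − 30 = 10 | 10 / 40 = 0.25 c |
| 3% | 5% | 50 − 30 = 20 | 20 / 40 = 0.5 c |
| 5% | 3% | 30 − 50 = −20 | −20 / 40 = −0.5 c |

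In every row the stated horizon counts no readmissions in either arm. Both the sign and the size depend on rates that the documents do not supply.

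**The case against.** The strongest reply has five parts.

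- **Antenatal costs are not excluded.** A reader might infer from a horizon starting at birth that the whole intervention cost is lost. The documents do not support that. The next sentences include drug, administration and attendance costs and treat post-birth costs as a separate component. This stands, and what remains is a conflict of wording.
- **Bias is not shown.** A reader might infer that the arm discharged sooner is automatically favoured. That does not follow, because only a difference in post-discharge cost matters (step 4). This stands. Nor does the number of days between an early discharge and day 28 measure the loss, since under hospital-record costing a day at home without hospital contact costs nothing.
- **The named harms mostly fall inside the window.** Hypoglycaemia is defined as diagnosed within 48 hours of birth, and maternal infection as arising during the hospital admission. This largely stands, so it would be wrong to say that these harms drop out of the costing.
- **The collection sentence may state a maximum.** Read that way, collection could stop at discharge and agree with the horizon. This is possible but not the natural reading, because the sentence has no discharge limit and sits beside clinical outcomes followed to 28 days. If it is what is meant, the sentence needs correcting.
- **An index-admission horizon is defensible, and details belong in a health economics plan.** Such a plan may well settle how twins with different discharge dates are handled. But the end of the horizon is a rule the article states, and it sits badly with the article's own collection window.

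The planned 2-year and lifetime model does not answer the point. It is built only if differences in effectiveness, costs or cost-effectiveness are found, and the cost part of that condition would rest on the truncated costs.

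**Conclusion.** The point holds as an avoidable omission. Followed as written, the primary within-trial horizon leaves out hospital costs between discharge and day 28 for the babies and the woman. Its cut-off is a post-randomisation event that treatment may change and that can differ between twins. Incremental cost is biased if post-discharge costs differ between arms. Whether they do, in which direction and by how much cannot be computed from the documents, and the table above only illustrates the mechanism on assumed rates.

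The conclusion rests on two readings: that the horizon is applied literally at discharge, and that resource use is collected to day 28 whether or not the child has gone home.

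The start at birth is a wording conflict to reconcile and does not mean that antenatal costs will be dropped. The primary clinical outcome and the sample size are not affected.

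**What to change.** Replace the horizon in the protocol and the health economics plan with: from randomisation to 28 days after birth, for the woman and both babies, regardless of discharge date. Cost all resource use planned for collection in that window, including readmissions, in both arms. Keep the birth-to-discharge version, with antenatal intervention costs added, as a sensitivity analysis. Starting at randomisation also removes the conflict with the antenatal cost sentences.

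This costs one sentence. If collection runs to day 28, as the section most naturally reads, no new data are needed. If collection in fact stops at discharge, correct the collection sentence and state plainly that post-discharge costs are excluded.

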### Internal pilot

There will be an internal pilot phase over the first 10 months of the trial when we aim to recruit 159 women and have 36 sites open. There is a clear stop/go traffic light criterion for trial progression beyond the internal pilot.

### Co-enrolment

Coenrolment in STOPPIT-3 and another non-interventional research study (eg, sample only or questionnaire studies) is permitted and this does not require any formal written documentation. This includes the related STOPPIT-3 mechanistic study (STOPPIT-M) sponsored by the NIHR Efficacy and Mechanism Evaluation (EME) programme (reference NIHR133388).

Coenrolment in STOPPIT-3 and another CTIMP or interventional non-CTIMP (eg, diagnostic, device or surgical interventions) are permitted provided an assessment on the safety of study participants, interventions involved, participant burden and the potential impact on the study endpoints have been considered. This assessment will be performed and documented in line with the Sponsor policy on coenrolment.

### Ineligible and non-recruited participants

Women who consent to participate in the study, but who spontaneously give birth or undergo IOL or CS prior to randomisation will not be eligible for randomisation. Such women who did consent to participate will be withdrawn but will remain on the eCRF system and reported in recruitment metrics as ineligible post consent. No delivery outcomes will be collected and they will continue receiving standard care under the management of a clinician, as per current guidelines. The woman’s care will not be affected due to non-trial participation. Randomisation and IMP administration should be performed contiguously to minimise the chance of spontaneous labour or delivery between randomisation and IMP administration.

### Unblinding

Breaking of the study blind will only be performed where knowledge of the treatment is essential for the clinical management of the woman or neonate. Unblinding is managed by the central Edinburgh team.

### Withdrawal of study participants

Patients are free to withdraw at any point or can be withdrawn by the investigator. The primary reason for withdrawal will be recorded in the patient’s eCRF and medical record.

### Trial management and oversight

The multisite trial will be coordinated by a Project Management Group consisting of the grant holders and the Trial Management Team within the ECTU. A Trial Steering Committee (TSC) will be established to oversee the conduct and progress of the trial. An independent data monitoring committee will be established to oversee the safety of participants in the trial.

### Patient and public involvement (PPI)

The study was designed in response to a recent global priority setting partnership of 1000 parents of twins who identified 10 research priorities for future health of multiples and their families. Two of the top 10 priorities will be addressed within STOPPIT-3: (1) How can we reduce multiples’ (the babies) admission to the NNU and can we reduce their length of stay in the NNU and (2) what are the short-term and long-term outcomes in multiple pregnancies and are these outcomes affected by antenatal events and medical interventions?

The study has been co-designed with two charities who represent parents with twins, the Twins Trust and the Elizabeth Bryan Multiple Birth Centre (formerly the Multiple Births Foundation). We consulted parents, through both charities at the grant submission stage and also at the protocol stage specifically on study design, the primary outcome and effect size, secondary outcomes and recruitment strategies.

Patients and the public are also involved in the TSC for this study with two individual patients as well as involvement of the coapplicants from the Twins Trust and the Elizabeth Bryan Multiple Birth Centre. A virtual parent advisory group has been set up to review patient facing materials and advice on dissemination plans. Individual study participants will be sent a summary of the study findings when the main study is published.

### Ethics and dissemination

The study will be conducted in accordance with the principles of the International Conference on Harmonisation Tripartite Guideline for Good Clinical Practice (ICH GCP). The results of the study, together with other mandated information, will be uploaded to the European clinical trials database within 1 year of the end of the study. Summaries of results will also be made available to investigators for dissemination within their clinics (where appropriate and according to their discretion). The results will be disseminated via publication in peer-reviewed journals and conference presentation and will also be communicated to the public via links with charity partners and social media.
